### Intervention

All eligible patients will be randomly allocated to one of the two following groups; the aspirin plus placebo group and aspirin plus metformin group. Endoscopists, doctors at the follow-up outpatient clinics and patients will be blinded to the groups. Patients in the aspirin plus placebo group will receive oral aspirin (100 mg) and placebo per day for 8 weeks, and patients in the aspirin plus metformin group will receive 100 mg of aspirin and 250 mg of metformin per day for 8 weeks. At the end of the 8 weeks of administration of a colonoscopy will be performed to evaluate the number of rectal ACF.

### Outcome measurements

The primary endpoint will be the change in the number of colorectal ACF after 8 weeks of treatment. A magnifying colonoscope will be used in all cases (H260AZI, PCF-Q260AZI, PCF-Q290AZI, HZ290; Olympus Co., Tokyo, Japan), with carbon dioxide insufflation. Bowel preparation for the colonoscopy will be initiated one day before the procedure. Each patient will be instructed to consume a low-residue diet and take 5 mg of oral sodium picosulfate on the evening before the procedure. On the day of the procedure, each patient will be given 1500 ml of polyethylene glycol (PEG). If the stools are not sufficiently clear, an additional 500 ml of PEG will be given to ensure sufficient bowel cleaning. For conscious sedation, midazolam and pentazocine will be administered at the beginning of the procedure. Intramuscular glucagon or scopolamine will be administered to reduce colonic movements. At the time of the first colonoscopy, the endoscope will be inserted into the cecum, and the entire colorectum will be carefully observed as the endoscope is pulled back. Rectal epithelial samples will be obtained. The number of rectal ACFs will be counted as follows. First, the rectum will be washed with warm water, then sprayed with 0.25% methylene blue solution and stained for 2 min, washed again with warm water, and finally examined by magnifying endoscopy for ACFs. At the end of 8 weeks of administration, the same endoscopists will perform the polypectomy and counting of the ACF. All procedures will be recorded on DVD, and all of the ACF will be photographed. The number of ACF in each patient will be counted by the endoscopists during the colonoscopy. To further ensure validity, the number of ACF will be counted again through observation of the recorded DVD by 3 blinded expert endoscopists ([name], [name] and [name]). If there was a discrepancy among the blinded specialists, we adopted the consent of at least two of the three. Additionaly if these expert endoscopists judge the colonoscopy examination as inadequate, that case will be excluded.

### Randomization

The investigator will repot the patient’s details to the central registration center via fax. After an eligibility check, the patients will be randomly assigned to receive aspirin plus placebo or aspirin plus metformin at the central registration center by a computer program that will block allocation by age and sex. In this way, the patient assignments will be concealed from the investigator. The randomization center will allocate a numbered treatment pack to each patient, which will contain all the drugs or placebos needed to complete a course of the trial treatment for one patient. Drug allocation was masked from all patients, endoscopists, doctors, and investigators until the end of the trial.

### Drug supply

Aspirin will be purchased from Bayer Pharma, Ltd. Metformin will be purchased from Dainippon Sumitomo Pharma Co., Ltd. The placebo (250 mg lactose) will be purchased from Kondo photo process Co., Ltd., Osaka, Japan. All trial drugs will be packaged identically and identified only by number. Subjects will be instructed to take two tablets of the trial drugs after breakfast each day. Compliance will be monitored by counting the empty drug packages returned by the patients at colonoscopy. The participants will be also interviewed and monitored that they had not used prohibited agents (aspirin, metformin and/or other non-steroidal anti-inflammatory drugs). If serious adverse events or less than 80% drug compliance are confirmed in a patient, that patient will be removed from the final analysis.

### Sample size estimation

We previously showed that metformin administered at 250 mg/d for 1 year suppressed metachronous adenoma and the effectiveness was similar to previous aspirin chemoprevention trials [8, 9, 16]. Based on these finding, we estimated that aspirin and metformin have similar chemopreventive effects on colorectal carcinogenesis. Then we estimated that the ACF number would change about − 3 ± 2 (mean ± SD) in the aspirin plus placebo group and − 5 ± 2 (mean ± SD) in the aspirin plus metformin group based on our previous metformin ACF prevention trial [15]. To detect the reduction in the number of ACFs in the two groups using the Student’s *t* test with a two-sided significant level of 5% and a power of 80%, it was found that a sample size of 17 to 26 patients in each group would be necessary. Assuming some patients would dropout, we propose to recruit a total of 60 patients with 30 patients in each group.

### Statistical analysis

The changes of ACFs number in each group, the primary endpoint, will be compared between the aspirin plus placebo group and the aspirin plus metformin group by the Student *t* test. The safety, one of the secondary endpoints, will be compared by the chi-square test. The remaining results in the two groups will be compared by the Mann-Whitney *U* test or the *t*-test. A *P* values of < 0.05 will be regarded as indicative of statistical significance. The analysis will be performed using SPSS statistics, version 26 (SPSS, Chicago, IL, USA).

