### Eligibility criteria

Patients with both colorectal ACF and resectable polyps will be recruited for this study. The inclusion criteria are as follows:
Patients with resectable polyps.Patients with more than 10 rectal ACF.Willingness to provide written informed consent.

The exclusion criteria are as follows:
Patients with lesions for which preferred early resection is preferred.History of regular use (defined as at least once per week) of NSAIDs and/or aspirin.History of regular use of warfarin and/or direct oral anticoagulants (DOAC).History of diabetes mellitus (defined as a glycosylated hemoglobin (HbA1c) level more than 6.5% or regular use of anti-diabetic drugs).History of heart failure, renal failure, liver cirrhosis or chronic hepatic failure.History of familial adenomatous polyposis, hereditary non-polyposis CRC and inflammatory bowel disease.Pregnancy or possibility of pregnancy.Contraindication to aspirin or metformin.Allergy to aspirin or metforminPatients judged as inappropriate candidates for the trial by the investigators.

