## Discussion

This is the first study proposed to evaluate the chemopreventive effect of aspirin and metformin combination therapy in patients with rectal ACF. Given its role as an analgesic, antipyretic and agent for cardiovascular prophylaxis, aspirin has become one of the most commonly used drugs. Many studies have provided considerable evidence demonstrating its potential for the prevention of CRC. Aspirin exerts its anticancer effects through several interconnected mechanisms, including prostaglandin synthesis and catabolism in epithelial cells [30, 31]; inhibition of WNT β-catenin signalling [32, 33]; inactivation of platelets [34, 35] and the host immune response [31, 36]. Aspirin may also act through several other unknown mechanisms. Furthermore, aspirin may has been hypothesized to act synergistically with other agents [37]. Further study is needed to clear the chemopreventive effect of aspirin. Metformin (1,1-dimethylbiguanide hydrochloride) is a biguanide derivative that is widely used for the treatment of diabetes mellitus [38]. Metformin activates AMPK, which inhibits the mammalian target of rapamycin (mTOR) pathway [39]. The mTOR pathway plays an important role in the regulation of cellular protein translational machinery and cell proliferation [40]. The best-characterized downstream effector of mTOR is S6 kinase, which regulates the initiation and elongation phases of translation [41]. Activation of the mTOR pathway has been shown to accelerate cell cycle progression from G1 to S in CRC DLD-1 cells [42]. Therefore, AMPK activation may inhibit cell growth and proliferation by suppressing protein synthesis, thereby having a potent antiproliferative effect. Recent evidence indicates that metformin has a suppressive effect on tumorigenesis and cancer cell growth [43–45]. In one study, metformin was demonstrated to activate AMPK and consequently decrease cellular proliferative activity, to produce a general decrease in protein synthesis in vitro in human breast carcinoma cells [43]. Metformin was also shown to inhibit the proliferation of human prostate cancer cells [45]. In addition, we performed a RCT and we showed that metformin reduced the incidence of new polyps in patients after polypectomy of the colon [16]. However, similar to aspirin, the chemopreventive effective was limited. In this study, we aim to evaluate the chemopreventive effect of aspirin and metformin combination therapy in patients with rectal ACF and determine whether the combined use of aspirin and metformin produces a stronger chemopreventive effect than each drug alone. Because we hypothesize that both aspirin and combination therapy may have a chemopreventive effect, a higher number of baseline ACFs (> 10) was needed to detect a difference between the two treatment effects. We previously reported a mean number of ACFs in adenomas of 6.2 ± 7.0 [24], which is why we set > 10 ACFs as an inclusion criterion. Consequently, we expect the trial to take longer because of the small number of patients who meet the inclusion criteria.

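### The primary t test on change in ACF count is valid but leaves out baseline ACF, age and sex; adjusting for them would probably gain precision at small cost

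*Protocol article*

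**What the plan says.** All of the following is in the protocol article.

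- **Outcome measurements:** "The primary endpoint will be the change in the number of colorectal ACF after 8 weeks of treatment". The rectal ACF count is taken at the baseline colonoscopy and again at 8 weeks.
- **Statistical analysis:** the changes "will be compared between the aspirin plus placebo group and the aspirin plus metformin group by the Student *t* test". No covariate is named.
- **Sample size estimation:** the same test, "with a two-sided significant level of 5% and a power of 80" per cent, with a mean change of minus "3 ± 2 (mean ± SD) in the aspirin plus placebo group" and minus "5 ± 2 (mean ± SD) in the aspirin plus metformin group". The stated need is 17 to 26 per group, and 30 per group are to be recruited.
- **Randomization:** assignment is made by "a computer program that will block allocation by age and sex". Baseline ACF is not an allocation factor.
- **Eligibility criteria:** "Patients with more than 10 rectal ACF". The Discussion explains the threshold by an earlier series: "We previously reported a mean number of ACFs in adenomas of 6.2 ± 7.0".

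**The concern.** A change score gives the baseline a fixed coefficient of 1. This is the best use of baseline only if the slope of the 8-week count on the baseline count is 1. The slope would fall below 1 if the count carries measurement error, or if treatment removes a proportion of lesions rather than a fixed number. Both are plausible for a count read from endoscopy in patients with many ACF.

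The change score then stays correlated with baseline. The t test leaves that explainable variation in its error term, and the arm that happens to start higher appears to improve more. Neither the design nor the analysis controls baseline ACF. Age and sex are controlled in allocation but not used in the analysis.

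Precision and robustness are at stake, not validity. The trial is small, and the Discussion expects slow recruitment because few patients qualify.

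**Working it through.** **Inputs.** Planned difference 2, change SD 2, two-sided 5%, 80% power, 30 per group (Sample size estimation). Assumption: baseline SD in eligible patients is about 7, the SD quoted in the Discussion for the earlier series. As a check on that value, a negative binomial with mean 6.2 and SD 7.0, truncated above 10, has SD 7.2. The slope b of the 8-week count on baseline is not given, so a range is shown.

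**1. The plan's own figure.** The normal approximation is n = 2(1.96 + 0.84)² × (2/2)² ≈ 15.7, so 16 per group. The exact noncentral-t calculation gives 17, the lower end of the stated range. Power of the t test is 80.7% at 17 and 96.8% at 30 per group. The upper end of 26 does not follow from SD 2; at 80% power it corresponds to SD 2.5, which the article does not state.

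**2. Residual variance after baseline adjustment.** The correlation of change with baseline is r = (b − 1) × SD(baseline) / SD(change). The ratio of adjusted to unadjusted residual variance is 1 − r².

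| Slope b | r = (b − 1) × 7/2 | 1 − r² |
|---|---|---|
| 1.00 | 0 | 1.00 |
| 0.95 | −0.175 | 0.97 |
| 0.90 | −0.35 | 0.88 |
| 0.85 | −0.525 | 0.72 |

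With baseline SD 7.2 the last two ratios become 0.87 and 0.71. A smaller baseline SD shrinks the gain, because r is proportional to it.

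**3. Chance imbalance.** The standard error of the baseline difference is 7 × √(2/30) = 1.81 ACF. Given a baseline difference D, the change-score estimate moves by (1 − b) × D in size. For a one-standard-error imbalance:

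- slope 0.9: 0.1 × 1.81 = 0.18 ACF, 9% of 2
- slope 0.85: 0.15 × 1.81 = 0.27 ACF, 14% of 2

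The standard error of the unadjusted treatment estimate is 2 × √(2/30) = 0.52, so the shift at slope 0.9 is about a third of it.

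**4. Cost and gain in power.** Adjustment for baseline alone takes one degree of freedom and multiplies the variance by 1 + 1/(2n − 4). It breaks even when r² = 1/(2n − 3), that is |r| = 0.18 at 17 per group and 0.13 at 30. With baseline SD 7 and change SD 2 these correspond to slopes of about 0.95 and 0.96.

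| Difference 2, SD 2 | 17 per group | 30 per group |
|---|---|---|
| t test | 80.7% | 96.8% |
| Adjusted, r = 0 | 79.3% | 96.5% |
| Adjusted, r of size 0.3 | 83.0% | 97.7% |
| Adjusted, r of size 0.5 | 89.4% | 99.2% |

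If the change SD is 2.5 and 26 per group are analysed, power is 80.7% for the t test and 89.8% with adjustment at |r| = 0.5.

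**5. Validity.** In simulations with the truncated negative binomial baseline (6,000 runs per case, blocking not modelled), both methods were unbiased. Type I error was 4.3% to 5.4% for the t test and 4.4% to 5.6% for the adjusted model.

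**The case against.** The strongest reply is that nothing here is wrong. The endpoint is a change, the sample size rests on a t test of that change, and the analysis is that t test. Power is about 97% at the planned inputs, and a supplementary adjusted analysis could sit in an analysis plan that is not shown. The coherence and validity stand. However, the article itself fixes the primary test. The 97% also needs SD 2 and all 30 per arm analysed, whereas the article removes inadequate colonoscopies (Outcome measurements) and patients with serious adverse events or compliance below 80% (Drug supply).

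A reader might infer more than the documents support:

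- **That the t test is biased because entry requires a high count.** Regression to the mean acts equally in both randomised arms and does not bias their comparison. Under a linear relation, truncating on baseline does not by itself push the slope below 1.
- **That a baseline imbalance of 1.8 rivals the effect of 2.** Only the fraction 1 − b of it reaches the estimate, and chance imbalance is already reflected in the t test's standard error.
- **That much larger gains or shifts apply.** A slope of 0.7 cannot hold with baseline SD 7 and change SD 2, because the change SD would have to be at least 0.3 × 7 = 2.1. If the two visits also had equal variances, then 4 = 2 × 49 × (1 − ρ) gives a correlation ρ of 0.96 and a variance ratio (1 + ρ)/2 of 0.98, a gain of only 2%.
- **That omitting age and sex invalidates the test.** If they predict the change, the test is conservative; the article does not say that they do.
- **That adjustment is free.** It spends degrees of freedom, assumes a common linear slope for skewed counts, and loses slightly when baseline hardly predicts change.

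**Conclusion.** The point holds as an efficiency and robustness improvement, not as an error or contradiction. Baseline adjustment is likely, though not certain, to be more precise than the planned test. With baseline SD about 7 (assumed) and change SD 2 (planned), the reduction in residual variance runs from nothing at slope 1 to 12% at slope 0.9 and 28% at slope 0.85. Its exact size cannot be settled from the article, because the slope is not given. The worst case considered, baseline unrelated to change, costs 0.3 percentage points of power at 30 per arm and 1.4 at 17, for baseline adjustment alone. The likely gain outweighs that cost, most clearly if the change SD proves larger than 2 or the analysed groups are well below 30.

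**What to change.** Before unblinding, make the primary analysis a linear model of the change in ACF count (or of the 8-week count) on treatment, with baseline ACF count, age and sex as covariates. Report the adjusted difference with its 95% confidence interval, and keep the Student t test as a supportive analysis. With baseline in the model, change and 8-week count as outcome give the same treatment estimate.

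This takes about one sentence in the protocol or analysis plan and no new data. With age and sex each entered as a single term, residual degrees of freedom at 60 patients fall from 60 − 2 = 58 to 60 − 5 = 55. Because the counts are skewed, the common linear slope should be checked and the check reported. The planned sample size need not change.

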### Trial steering committee and data monitoring committee

The Trial Steering Committee and Data Monitoring Committee will be located in the Department of Gastroenterology and Hepatology at Yokohama City University Hospital. The Management Team will monitor the trial progress status and data by face-to-face and/or telephonic contact with each of the trial investigators every month.

### Study flow

A flow chart of the study is shown in Fig. 1.

**Fig. 1 Fig1:**
[figure not shown]
Study Flow

## Discussion

This is the first study proposed to evaluate the chemopreventive effect of aspirin and metformin combination therapy in patients with rectal ACF. Given its role as an analgesic, antipyretic and agent for cardiovascular prophylaxis, aspirin has become one of the most commonly used drugs. Many studies have provided considerable evidence demonstrating its potential for the prevention of CRC. Aspirin exerts its anticancer effects through several interconnected mechanisms, including prostaglandin synthesis and catabolism in epithelial cells [30, 31]; inhibition of WNT β-catenin signalling [32, 33]; inactivation of platelets [34, 35] and the host immune response [31, 36]. Aspirin may also act through several other unknown mechanisms. Furthermore, aspirin may has been hypothesized to act synergistically with other agents [37]. Further study is needed to clear the chemopreventive effect of aspirin. Metformin (1,1-dimethylbiguanide hydrochloride) is a biguanide derivative that is widely used for the treatment of diabetes mellitus [38]. Metformin activates AMPK, which inhibits the mammalian target of rapamycin (mTOR) pathway [39]. The mTOR pathway plays an important role in the regulation of cellular protein translational machinery and cell proliferation [40]. The best-characterized downstream effector of mTOR is S6 kinase, which regulates the initiation and elongation phases of translation [41]. Activation of the mTOR pathway has been shown to accelerate cell cycle progression from G1 to S in CRC DLD-1 cells [42]. Therefore, AMPK activation may inhibit cell growth and proliferation by suppressing protein synthesis, thereby having a potent antiproliferative effect. Recent evidence indicates that metformin has a suppressive effect on tumorigenesis and cancer cell growth [43–45]. In one study, metformin was demonstrated to activate AMPK and consequently decrease cellular proliferative activity, to produce a general decrease in protein synthesis in vitro in human breast carcinoma cells [43]. Metformin was also shown to inhibit the proliferation of human prostate cancer cells [45]. In addition, we performed a RCT and we showed that metformin reduced the incidence of new polyps in patients after polypectomy of the colon [16]. However, similar to aspirin, the chemopreventive effective was limited. In this study, we aim to evaluate the chemopreventive effect of aspirin and metformin combination therapy in patients with rectal ACF and determine whether the combined use of aspirin and metformin produces a stronger chemopreventive effect than each drug alone. Because we hypothesize that both aspirin and combination therapy may have a chemopreventive effect, a higher number of baseline ACFs (> 10) was needed to detect a difference between the two treatment effects. We previously reported a mean number of ACFs in adenomas of 6.2 ± 7.0 [24], which is why we set > 10 ACFs as an inclusion criterion. Consequently, we expect the trial to take longer because of the small number of patients who meet the inclusion criteria.

This trial may have the following limitations. First, ACFs are considered as a reliable surrogate biomarker of CRC [22], although their biological significance still remains controversial. However, setting study endpoint as ACF has large merit to reduce efforts because ACFs are quantitative and it is possible to observe changes in a short period of time. Thus, we devised a trial using ACF as the primary endpoint to evaluate the chemopreventive effects of aspirin and metformin combination therapy. Second, an intervention period of 8 weeks may be too short to allow the reliable detection of differences between the groups. However, we showed in a previous study that oral administration of metformin for 1 month suppressed the formation of colorectal ACF in humans. Other reports show that ACFs decrease in number in 8 weeks with the use of NSAIDs [23]. Therefore, we think that an intervention period of 8 weeks would be sufficient to evaluate the changes in the number of ACF. We previously conducted a short-term chemoprevention trial of metformin for colorectal ACF, and we showed the suppressive effect of the drug on the formation of ACF. Thereafter, we conducted a long-term metformin chemoprevention trial for colorectal polyps. We propose to repeat the same steps for the chemoprevention trial to investigate the combined use of aspirin and metformin. Third, our study lacks dose-response data. However, low-dose aspirin (100 mg/d) is used worldwide with reported chemopreventive effects on CRC and adenoma. Furthermore, we previously reported the effect of low-dose metformin (250 mg/d) on colorectal adenoma and ACF. Finally, our study lacks a metformin alone arm and double placebo arm, while the use of aspirin alone has not been established to suppress to the formation of ACFs. However, aspirin is one of the most efficiacious chemopreventive agents for the treatment of colorectal adenoma and CRC, which is why we used aspirin alone as the control arm in the present study. A four-arm study using a double placebo is needed in the future to investigate the combination effect of metformin and aspirin.

If this combination therapy was found to be more effective for the prevention of CRC, the impact would be significant. Therefore, we consider it of interest to determine whether the combined use of aspirin and metformin shows a stronger chemopreventive effect on the formation of human colorectal ACFs than either aspirin or metformin alone.

